## Abstract

Emotional disorders (ED) such as anxiety, depression and somatization are extremely prevalent disorders that can affect an individual’s quality of life and functionality. Primary Health Care (PHC) is the first place to identify most patients with these conditions. Mental health services in the Dominican Republic, as well as in Latin America and the Caribbean in general, are unable to provide appropriate care for most people with mental disorders. Using evidence-based treatment protocols is also crucial to make progress in helping people with ED. The PsicAP project is a group intervention that uses a transdiagnostic approach and is grounded in cognitive-behavioral techniques. The program is implemented in 7 group sessions, each lasting for one and a half hours. The program has been shown to be effective in reducing clinical symptoms, dysfunction, and in improving quality of life. It is also a non-time-intensive, low-cost treatment that is helpful for addressing EDs in a PHC context. The objective is to bring psychological treatments into PHC facilities of Dominican Republic, making them more accessible for a larger amount of the population.

## Background

Emotional disorders (ED) such as anxiety, depression and somatization are extremely prevalent disorders that can affect an individual’s quality of life and functionality [1]. The individuals who suffer from these disorders are not the only ones whose lives are affected; families and society in general also suffer due to the heavy burdens and socio-economic effects associated with EDs (2–3).

According to data from the World Health Organization [3], in 2015 more than 300 million people around the world suffered from depression (representing approximately 4.4% of the global population), while 264 million suffered from anxiety (equivalent to approximately 3.6% of the global population). After the onset of the COVID-19 pandemic, ED cases increased significantly due to factors such as social isolation, the death of close friends and family members, fear of infection and financial problems caused by the pandemic [4]. It is estimated that there may have been an additional 53.2 million cases of major depression around the world in 2020, as well as 76.2 million cases of anxiety disorders [5].

Specifically in the Dominican Republic, 464,164 people (4.7% of the country’s population) suffered from depressive disorders in 2015, while 570,312 (5.7% of the national population) suffered from anxiety disorders [3]. Following the onset of the pandemic, as in the rest of the world, there has been a significant increase in new cases of this type of ED in the country [6]. Despite this, the mental health centers and services in the Dominican Republic, as well as Latin America and the Caribbean in general, have not been bolstered in such a way where they can respond efficiently and effectively to the significant surge and increased prevalence of EDs. The lack of physical locations, financial resources, mental health professionals in Primary Health Care facilities or implementation of protocols to prevent and treat EDs continues to be a significant issue for the country [7].

If not addressed appropriately and in a timely manner, the chronicity, comorbidities and disabilities associated with EDs tend to increase [8]. Most patients do turn to PHC services for support and treatment. However, in these centers they are cared for by health professionals that are not appropriately trained for these types of psychological disorders [9]. As a result, patients are often under- or inappropriately diagnosed, leading to poor or inadequate treatment. Likewise, the lack of protocols and personnel trained to address mental health issues in PHC facilities leads to an additional outcome, where patients tend to be treated exclusively with psychotropic drugs. These medications do not solve the root of the problem or help patients manage their emotions, behaviors or thoughts, which can lead to chronic ED. Additionally, in the long term, psychotropic drugs can be addictive and toxic to the body, and can also cause an increase in traffic-related and domestic accidents (10–11).

Cognitive Behavioral Techniques (CBT) have shown that effective intervention strategies do exist to treat emotional disorders in both the child and youth populations, as well as in adults [12]. Using these strategies, individuals are able to identify their emotions, thoughts and behaviors while learning how to manage and restructure them. During the therapeutic process, the patient develops skills that enable them to recognize triggering situations and identify more adaptive behaviors that will help them develop strategies to face their difficulties more effectively [13–16]. Because of its effectiveness, CBT is the treatment of choice for various mental health care systems around the world [15].

Also, implementing CBT using a transdiagnostic model (approaching EDs as a unit with common characteristics and backgrounds) has been shown to be effective in reducing emotional symptoms [17–20] while also providing significant improvement in cost-effective and cost-utility relationships [21]. In fact, the transdiagnostic approach allows individuals with different but related emotional disorders to be grouped together [17], making it possible to save professional, economic and time-related resources when compared to individual and non-transdiagnostic therapies (13, 21–22).

In countries like England and Spain, it has been proposed that psychological therapy be included in PHC services in order to ease the aforementioned impacts and improve the mental health of the population [23]; furthermore, the cognitive-behavioral transdiagnostic protocol known as PsicAP was developed in Spain. A randomized controlled trial with 1,691 patients showed that group-administered transdiagnostic CBT was effective in reducing emotional symptoms [14]. Patients who participated in the PsicAP protocol in the intent-to-treat analyses showed a reduction in their anxiety (d = -0.65), depression (d = -0.58) and somatic symptoms (d = -0.40). These effects were also maintained after 12 months of follow-up.

In light of the favorable results obtained by the PsicAP protocol in Spain, the main purpose of this study is to replicate the same clinical trial in the Dominican Republic. Carrying out the PsicAP clinical trial in the Dominican Republic (ClinicalTrial.gov ID: NCT04642092) is a potentially beneficial alternative for country’s mental health in terms of improving life satisfaction, academic, occupational and social well-being, as well as overall quality of life for affected individuals [16]. In addition to the specific benefits for the patients, this improvement could also lead to positive effects for their families and society as a whole, while making better use of government health service financial and time resources, including those of PHC facilities (24–25).

## Objectives

### Main objective

The main objective is to undertake a randomized clinical trial to evaluate the effectiveness of a group cognitive-behavioral transdiagnostic intervention (PsicAP) compared to the typical PHC treatment for ED patients in the Dominican Republic at 3 months, and to explore if results are maintained over time (6 months). The main outcomes will include decreased symptoms of anxiety, depression and somatization, as well as remission of potential cases of ED.

### Secondary objectives

To explore the efficacy of this new treatment compared to the traditional PHC treatments that are offered as a means of reducing dysfunction and improving quality of life, at 3 months.To explore the efficacy of the new treatment compared to traditional PHC treatments in reducing risk factors for cognitive distortions and emotional regulation strategies.To study the level of satisfaction with the treatments received.To develop a digital platform that includes content related to education, relaxation, cognitive/behavioral techniques and emotional regulation strategies for the general population and to provide additional training to therapists.

### Hypotheses

The hypotheses derived from the study objectives are that, in post-treatment and continuing through follow-up, patients who participate in the transdiagnostic cognitive-behavioral group treatment (PsicAP), as compared to the control group receiving typical treatment, will experience:

A more noticeable decrease in anxious, depressive and somatic symptoms.Higher rates of remission when screening for possible anxiety, depressive and somatic disorders.Better work, social, and domestic functioning.A better quality of life.A more noticeable decrease in risk factors for cognitive distortions and emotional regulation strategies.

### Study design

This is a randomized, controlled, two-armed clinical trial, with one arm consisting of the control group that will receive usual PHC treatment and another consisting of the experimental group receiving treatment according to PsicAP protocol. It should also be clarified that this is a simple blind trial, specifically in the fact that the evaluators are not the same psychologists as those giving the treatment. However, the study will not be blind in some respects, as patients can guess which group they belong to (since it is not possible to blind this condition), as will the therapists. Study participants will be assessed at 6 and 12 months after the seventh study session.

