## Therapist training

Each PsicAP group is led by a therapist who is also working together with a co-therapist. All of the therapists who are assisting the patients in the Dominican Republic PsicAP project originally graduated with a Bachelor’s degree in psychology, which requires approximately 4 years of university training. One of the basic requirements for taking on a therapist role was also to have a master’s degree in clinical psychology or a related area. Some of the therapists also have a Ph.D. in psychology. Co-therapists have a degree in psychology but have not yet completed a master’s program. The latter received specialized training so they could carry out the initial and final project assessments and assist the therapists appropriately during the sessions.

In order to standardize the therapeutic model to be followed, two significant types of training were done: (1) each therapist had to take an online course on the in TEA platform, which consisted of 45 h of training to refresh themselves on how to manage anxiety disorders (course name: “Refresher on the treatment of anxiety disorders: a cognitive-emotional and transdiagnostic approach” [*“Actualización en el tratamiento de los trastornos de ansiedad: un enfoque cognitivo-emocional y transdiagnóstico”*]); (2) therapists and co-therapists met once a week for seven weeks in order to share the slides and resources from each of the sessions that would be given to the participants, in an effort to establish guidelines so that the therapy in each of the centers would be as homogeneous as possible.

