## Data collection

After signing the informed consent, the participants are registered in the PsicAP database using alphanumeric codes to keep their identities anonymous. Participants perform pre- and post-treatment assessments digitally using computerized systems. All pre-treatment assessments are done at the centers along with the co-therapist, using tablets that can connect to the internet. The data that is collected is stored on the Survey Monkey platform (surveymonkey.com). The same battery of tests applied at the beginning of the treatment is administered upon completion. Ideally this last battery is also completed at the center together with the therapist, in the same fashion as during the pre-treatment phase. However, the participant will be given the option to complete it on their mobile device via WhatsApp or email using a link provided by the co-therapist. In this case, the co-therapist has the right to contact the participants via telephone in order to remind them to complete the post-treatment and follow-up evaluations.

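### The single-blind label rests on evaluators being separate from treaters, but the article assigns assessment to members of the treatment delivery team

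*Protocol article*

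**What the plan says.** Four statements in the protocol article bear on who assesses and who treats.

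- **Study design** gives the single-blind label and its only ground: "the evaluators are not the same psychologists as those giving the treatment". The same paragraph concedes that "patients can guess which group they belong to" and that therapists are not blind either.
- **Therapist training** describes delivery: "Each PsicAP group is led by a therapist who is also working together with a co-therapist". It adds that co-therapists were specially trained so they could "carry out the initial and final project assessments and assist the therapists appropriately during the sessions".
- **Data collection**, before treatment: "All pre-treatment assessments are done at the centers along with the co-therapist".
- **Data collection**, after treatment: "Ideally this last battery is also completed at the center together with the therapist". That sentence goes on to liken the arrangement to the pre-treatment one. The alternative is remote completion on the patient's own device, through a link that the co-therapist supplies. The co-therapist may also telephone reminders for the post-treatment and follow-up batteries.

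Data analysis names the GAD-7, PHQ-9 and PHQ-15, compared from baseline to post-treatment, as primary outcomes. Limitations lists the use of self-report, but not the presence of treating staff at assessment.

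**The concern.** A single-blind label tells readers and risk-of-bias assessors that outcome assessment was insulated from knowledge of the allocation. Here the insulation is said to come from separating evaluators from treaters, and the procedures do not provide that separation.

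The consequence goes beyond wording. All three primary outcomes are questionnaires that the patient answers. After seven weekly group sessions, a PsicAP patient may complete them beside, or after a reminder from, someone on the team that delivered the treatment. Control patients receive usual care from the primary care physician, so they have no comparable treatment relationship with these staff. Any tendency to report improvement out of courtesy would therefore act more strongly in the PsicAP arm and favor the intervention. The primary comparison uses the post-treatment battery, where this exposure is greatest.

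**Working it through.** **Comparing the statements.** The article contests no figure here, so the check is mainly textual.

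1. Study design: the label requires evaluators and treaters to be different people.
2. Therapist training: every PsicAP group has a therapist and a co-therapist, and co-therapists are also the trained assessors. The assessing role and the session role meet in one staff group.
3. Data collection, final battery: if therapist is meant literally, the preferred companion at the final assessment is the treater. If it stands for co-therapist, as the comparison with the pre-treatment phase suggests, the companion is still from the delivery team.
4. Data collection, remote route: the link and the reminders come from the co-therapist.
5. The article nowhere describes an assessor outside the delivery team or one unaware of allocation.

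Under both readings of step 3, the condition in step 1 is not met.

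**Scale, as illustration only.** Assumptions that are not in the documents: a courtesy shift of 1 point on the GAD-7 or PHQ-9, and an SD of 4 to 5 points. Inputs from Background: Spanish trial effects of 0.65 (anxiety) and 0.58 (depression), in absolute value.

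- Standardized shift = 1/SD: 1/5 = 0.20 and 1/4 = 0.25.
- Against anxiety: 0.20/0.65 = 31% and 0.25/0.65 = 38%.
- Against depression: 0.20/0.58 = 34% and 0.25/0.58 = 43%.

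**Effect on false positives, also illustrative.** Input from Patient recruitment: 150 per arm. Assumptions: no true effect, two-sided alpha of 0.05, and a simple comparison of two means by normal approximation, without baseline adjustment or clustering. In SD units SE = √(2/150) = 0.1155. For a setting bias b, the rejection probability is 1 − Φ(1.96 − b/SE) + Φ(−1.96 − b/SE).

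| Assumed b (SD) | Rejection probability |
|---|---|
| 0.05 | 7.2% |
| 0.10 | 13.9% |
| 0.15 | 25.5% |
| 0.20 | 41.0% |
| 0.30 | 73.8% |

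The table shows how sensitive a trial of this size would be to a small systematic shift. It does not estimate the shift.

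**The case against.** The strongest reply has three parts.

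*The roles can be read apart.* Therapists lead the groups and hold a master's degree; co-therapists assist. The psychologists giving treatment could mean the lead therapists only, and no statement says that a co-therapist assesses patients from his or her own group. This stands in part: a reader might infer that each patient is assessed by the very person who treated them, and the article does not say so. But co-therapists work inside the sessions, nothing keeps them from knowing the allocation, and no rule separates them from their own patients.

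*Most of the bias is already disclosed.* Staff do not rate the outcomes, patients are conceded to be unblinded, and self-report is listed as a limitation. This also stands. Bias from unblinded patients would remain with any evaluator. Only the added effect of staff presence is new, and its size is unknown.

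*A condensed article leaves out detail.* This does not help, because the difficulty lies in positive statements that conflict, not in an omission.

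Two further inferences are tempting but lack support. One is that controls would more often use the remote link, so that mode differs by arm. Data collection gives one procedure for all participants and reports nothing by arm. The other is that controls feel no pressure at all. The article does not say who sits with them at the final assessment, so less pressure is the most that can be argued.

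**Conclusion.** The stated basis for single blinding does not hold, and the label should not be reported. This rests on the article's text alone and needs no assumption about what therapist means in Data collection.

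The self-reported primary outcomes are open to added courtesy bias in the PsicAP arm. Its direction is plausible, but its size cannot be estimated from the documents. The illustrative 0.20 to 0.25 depends wholly on the assumed 1-point shift and SD of 4 to 5. A reader might set that shift against the smallest cited effect, 0.40, and conclude that it is half or more of what the trial expects. That comparison is not valid: 0.40 is the somatic-symptom effect, while the shift is on the anxiety and depression scales, where the fractions are 31–38% and 34–43%.

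Nor would reassigning assessors restore a single-blind claim. A co-therapist from another group is not thereby unaware of allocation, and the patients who score the outcomes can tell their own arm.

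**What to change.** 1. Reconcile Study design, Therapist training and Data collection so that they give one account of who assesses whom.
2. In Study design, drop the single-blind claim and describe the trial as open-label with unblinded, self-reported outcomes. This applies equally to data already collected.
3. In Data collection, for assessments still to be done, have both arms self-complete the post-treatment and follow-up batteries in the same mode, through the existing tablet or link, with no therapist or co-therapist who treated that patient present. Where help or a reminder is needed, use an existing co-therapist who did not treat the patient.
4. Record the mode of completion and the helper for each battery, to allow a sensitivity analysis.

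The wording change costs almost nothing. The procedural change uses tools already in place but needs some rescheduling of co-therapists across the six centers; the article does not give their number. Limitations notes lower education levels among these patients, so some may find completion without familiar staff harder, with a risk of more missing data. Recruitment began in August 2021 and post-treatment evaluations were expected to finish by May 2023, so for many patients only the corrected description may still be possible.

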## Data analysis

Intention-to-treat (ITT) analysis will be performed. The ITT analysis will include all randomized patients in the groups to which they were randomly assigned. Analysis will take into account noncompliance, protocol deviations, dropouts, and anything else that happens after randomization. The two randomized groups will be compared in the treatment period; posttreatment; and at 3 and 6 months after treatment finalization. In addition, within-subject comparisons will be analyzed, contrasting pretreatment and posttreatment scores. The within-group and between-group differences will be examined using mixed-effect models, since these are considered more accurate than univariate and multivariate repeated measures of variance. Group differences will be analyzed after controlling for baseline levels, gender, age, and treatment center. Analysis will be carried out using SPSS version 21.0 (IBM Corp).

For primary outcomes, will consider group differences in anxiety (GAD-7), depression (PHQ-9), and somatic symptoms (PHQ-15) comparing baseline and post-treatment scores using a mixed-effect model. For secondary outcomes, will check between-group differences in the level of disability on daily life domains (work, social, and family life) and quality of life domains (physical, psychological, social, and environmental). The effect sizes of the treatment on primary and secondary outcomes (mean scores) will calculate by applying Morris’s d statistic, where the standardized effect of the treatment is defined as the difference between groups in mean PPC values, divided by the common standard deviation. In addition, a per-protocol (PP) analysis for primary and secondary outcomes will performer only in the patients who completed all follow-up measurements.

Finally, will calculate additional analyses: recovery, reliable recovery, and deterioration rates. The recovery index was defined as pre- treatment scores above the threshold on any of the three scales and below the threshold on all scales at either the post-treatment or 6-month follow-up assessment. The reliable recovery rate will calculate using a change score based on the standard deviation (S.D.). Thus, will use a change score of ≥5 for the GAD-7 and ≥6 for the PHQ-9 and the PHQ-15.

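### Follow-up times in the study design do not match the objectives and analysis, and the primary model tests a different time from the main objective

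*Protocol article*

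**What the plan says.** The protocol article gives assessment or comparison times in several places.

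- **Main objective:** effectiveness is evaluated "at 3 months, and to explore if results are maintained over time (6 months"). It does not say whether months run from randomization, the first session or the end of treatment.
- **Secondary objectives:** the new treatment is explored "as a means of reducing dysfunction and improving quality of life, at 3 months".
- **Hypotheses:** the benefit is expected "in post-treatment and continuing through follow-up", with no months given.
- **Study design:** "Study participants will be assessed at 6 and 12 months after the seventh study session".
- **Data collection:** the baseline battery is repeated when treatment is completed. Follow-up evaluations are mentioned without dates.
- **Data analysis:** the arms are "compared in the treatment period; posttreatment; and at 3 and 6 months after treatment finalization". The primary outcomes (GAD-7, PHQ-9, PHQ-15) are analysed by "comparing baseline and post-treatment scores using a mixed-effect model". Recovery requires scores "below the threshold on all scales at either the post-treatment or 6-month follow-up assessment".

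**The concern.** There are two separate contradictions.

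1. **Follow-up schedule.** The design sentence gives 6 and 12 months. The Main objective and the Data analysis section give 3 and 6 months, and the first secondary objective gives 3 months. A site that took its follow-up visits from the design sentence would not collect the 3-month data that the objectives and analysis need. It would collect 12-month data that no objective or analysis uses.

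2. **Primary time point.** The Main objective puts the effectiveness question at 3 months. The primary model answers it at post-treatment. The trial's main question therefore has no single agreed time, and whichever time is reported as primary could be settled after the results are known.

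**Working it through.** **Step 1. Times side by side.**

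| Section | Times after baseline |
|---|---|
| Main objective | 3 months; 6 months (exploratory) |
| Secondary objectives (dysfunction, quality of life) | 3 months |
| Hypotheses | Post-treatment and follow-up, undated |
| Study design | 6 and 12 months after session seven |
| Data analysis, group comparisons | Treatment period; post-treatment; 3 and 6 months after treatment |
| Data analysis, primary model | Post-treatment |
| Data analysis, recovery index | Post-treatment or 6 months |

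Among the Main objective, Study design and Data analysis sections, month 6 is the only follow-up month in common. Month 3 is absent from Study design, and month 12 appears only there. If the Main objective counts from the end of treatment, it agrees with Data analysis on 3 and 6 months, and Study design is the single outlier.

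**Step 2. Can 3 months and post-treatment be the same visit?** The experimental treatment is seven sessions, one per week, so session seven falls 7 − 1 = 6 weeks after session one. Three months is 3 × (365.25 / 12) / 7 = 13.0 weeks.

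- Counted from session one, 3 months falls 13 − 6 = about 7 weeks after treatment ends.
- Counted from the end of treatment, it falls at about week 6 + 13 = 19.
- Counted from randomization, it would coincide with post-treatment only if about 13 − 6 = 7 weeks passed between randomization and session one. The article states no such wait.

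On the stated schedule, then, the post-treatment battery is not a 3-month assessment.

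**Step 3. Is there an assessment during treatment?** Data analysis lists a comparison in the treatment period. Data collection describes only pre-treatment, post-treatment and follow-up evaluations. This is a minor loose end, but the same edit can settle it.

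**Step 4. Size of the choice between two times.** Let Z1 and Z2 be the test statistics for one outcome at post-treatment and at 3 months, standard bivariate normal under no effect with correlation r, each tested two-sided at 5%. The article gives no r, so 0.6 to 0.7 is an assumption. The chance that at least one test is significant is 1 − P(|Z1| < 1.96 and |Z2| < 1.96).

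- r = 0.6: 8.8%
- r = 0.7: 8.3%

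The limits are 5% at r = 1 and 1 − 0.95² = 9.75% at r = 0.

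The stated sample size (150 per group) is tied to no time point, so this point does not bear on it.

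**The case against.** **The design sentence may be only a partial schedule.** It also omits the baseline and post-treatment assessments described under Data collection, and Data analysis plainly intends a 3-month comparison. This stands. A reader might infer that the 3-month data will never be collected, but the article does not establish that. It shows only that the dated follow-up sentence leaves out a visit that the analysis requires.

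**The follow-up times may not be stated in three incompatible ways.** This also stands, since the Main objective and Data analysis can agree on 3 and 6 months. What remains is one discordant sentence on the schedule and, separately, a mismatch between the objective and the primary model.

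**Six months is not a rival primary time.** The Main objective labels it exploratory, and no section offers it as primary. Counting three candidate times would overstate the error. So would multiplying by the three primary scales, because having several primary outcomes is a different issue that would remain after the times are reconciled.

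**A separate analysis plan could settle the matter.** It could select a time point, but it could not make this article's sections agree. These are conflicting statements, not details left out of a condensed article.

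**Conclusion.** Both contradictions hold on the text, and no other section resolves them. The follow-up sentence in Study design conflicts with the objectives and the analysis. The Main objective and the primary model name different times, and weekly sessions with a battery at completion do not bring those times together.

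The practical risk is a missed 3-month visit and an unanalysed 12-month one. The statistical risk is a free choice between two primary times, worth about 8–9% in place of 5% for one outcome. That figure assumes a correlation of 0.6 to 0.7 and a choice made after seeing results. The article does not suggest that such a choice is planned, and the contradictions stand without the figure.

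**What to change.** State one primary time point and one assessment schedule, each with its anchor (randomization or end of treatment). Use them in the same form in the Main objective, Secondary objectives, Study design and Data analysis. The anchor should also work for the usual-care arm, which has no seventh session.

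The least disruptive choice is:

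- **Primary time point:** post-treatment, which fits the Hypotheses and the existing primary model.
- **Follow-up:** 3 and 6 months after the end of treatment.
- **Main objective and first secondary objective:** reword the 3-month references to match.
- **Study design:** either replace 6 and 12 months with 3 and 6 months, or keep the 12-month assessment and add it to Data analysis.
- **Data analysis:** delete the comparison in the treatment period unless an assessment takes place then.

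The cost is more than wording. The Results section says recruitment began in August 2021, so the sponsor must first confirm which visits are actually being run. If sites have followed 6 and 12 months, the 3-month visits already missed cannot be recovered. Making post-treatment primary also changes the stated main objective of a running trial, so the change and its reason must be documented before outcome data are examined.
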